## Abstract

**Background::**

Knee osteoarthritis (KOA) is a common disease in elderly individuals. Many medications for KOA have the potential to cause side effects. We used *Juglandis semen* complex extract (JCE) consisting of 4 herbs derived from Cheong-A-Won, which has been commonly used for KOA treatment. In this study, we will evaluate whether JCE improves symptoms in patients with KOA and will identify the changes in the inflammation factor.

**Methods::**

This study will be a single-center, randomized, double-blind, and placebo-controlled trial. Three groups, JCE 1000 mg, 2000 mg, and placebo, will be randomly allocated. Total duration of the clinical trial will be 12 to 14 weeks. Study participants will be followed up every 6 weeks and the effect and safety will be assessed at the 2^nd^, 3^rd^, and 4^th^ visit. All participants were asked to maintain a dosage schedule for this protocol. The primary outcomes will be measured using Korean Western Ontario and McMaster Universities Questionnaire and the secondary outcomes will include pain Visual analog scale score, EuroQol Five Dimensions questionnaire, Patient Global Impression of Change, and the changes in the laboratory test parameters of inflammation. Repeated-measure analysis will be used to measure primary efficacy based on full analysis set.

**Discussion::**

This study has limited inclusion and exclusion criteria and a well-controlled intervention, and it will be the first randomized controlled trial to assess the efficacy and safety of JCE in patients with KOA. This study provides insights into the mechanisms that explain the therapeutic effects of JCE in KOA and will lay the groundwork for further studies.

## Introduction

1

Knee osteoarthritis (KOA) is a major cause of knee joint pain and is very common in elderly individuals. The symptoms of KOA are characterized by pain, inflammation, and stiffness in the musculoskeletal system, which ranges from localized self-limiting conditions to systemic autoimmune processes.^[1]^

The treatment of KOA is divided into conservative and surgical treatment. Basically, the symptom of pain is managed by conservative treatments such as hyperthermia, exercise therapy, and medication. However, if there is severe pain without improvement, joint deformity, instability, and limitation of movement, then surgical treatment such as osteotomy, arthroscopic surgery, and artificial joint replacement should be considered.^[2]^

In this study, we will try to prepare *Juglandis semen* complex extract (JCE) from *Juglandis semen*, *Eucommia ulmoides*, *Acanthopanax sessiliflorum*, and *Zingiber officinale*. This extract is referred to as “Cheong-A-won,” which was first recorded in “Tae-pyung-hye-min-hwa-je-kook-bang.” “Cheong-A-Won” is composed of *Juglandis semen*, *Eucommia ulmoides*, *Psoralea corylifolia*, and *Zingiber officinale*. Among these, *Psoralea corylifolia* is effective in promoting osteoblast proliferation and has been widely used in bone diseases.^[3]^ However, in this study, *Acnthopanax sessiliflorum*, safe for use in humans and widely used in conditions of the musculoskeletal system, was used instead of *Psoralea corylifolia* because there is a controversy about liver damage due to a toxic component of it.^[4]^ In the present study, the protocol was designed to verify the efficacy of JCE for symptoms of patients with KOA using a single-center, randomized, controlled, and double-blind clinical trial.

## Methods

2

### Study design

2.1

This study has been designed as a double-blind, single-center, randomized clinical trial for investigating the efficacy of JCE in KOA. A total of 36 subjects with KOA will be recruited from outpatients at the Daejeon University Cheonan Korean Medicine Hospital through advertisements posted on bulletin boards at hospitals, apartments, and so on. Recruitment commenced in April 2019, and the trial is expected to end in October 2019. All participants will receive a full written explanation of the study's protocol and an informed consent form. x-ray imaging of both knees will be performed for those who are suspected to have KOA based on history or physical examination. Additionally, blood tests for blood clotting factors, liver function, inflammation-related enzymes, and complete blood count will be performed. A total of 36 patients with knee pain who meet the eligibility criteria for this study will be randomly assigned in a 1:1:1 ratio to the treatment group 1 (JCE 1000 mg), treatment group 2 (JCE 2000 mg), or control group (placebo). The intervention will begin within 2 weeks of the screening visit. Based on the study group, the subjects will be administered JCE 1000 mg, JCE 2000 mg, or placebo for 12 weeks. The total duration of the clinical trial will be 12 to 14 weeks. Subjects will be followed up every 6 weeks, and the efficacy and the safety will be assessed at the 3^rd^ and 4^th^ visits. The study flow chart is presented in Figure 1.

**Figure 1 F1:**
[figure not shown]
Study design for JCE clinical trial. The treatment or control groups will be administered JCE 1000 mg or JCE 2000 mg or placebo. The subjects will receive JCE 1000 mg or JCE 2000 mg or placebo for 12 weeks and will visit every 6 weeks. JCE = *Juglandis semen*.

### Inclusion and exclusion criteria

2.2

The inclusion criteria are as follows: age, 40 to 75 years; knee pain for ≥6 months; grade 1 or 2 on the Kellgren-Lawrence grading scale on both knee x-ray examinations; whether the subject is taking arthritis medication such as non-steroidal anti-inflammatory drugs (NSAIDs), those who have not changed their medication within the last a month.

The exclusion criteria are as follows: KOA owing to factors like gout and rheumatism other than degenerative; history of fractures of the lower limb in the last 3 months; intra-articular injection of hyaluronic acid or steroids within 3 months of the study; continuous intake, 1 month before the study, of steroids or NSAIDs that may affect KOA; severe gastrointestinal symptoms such as heartburn and indigestion; alcohol abuse; clinically significant cardiovascular, immune, infectious, and/or neoplastic diseases other than arthralgia; suspected liver, kidney, or blood disease; habitual administration of psychotropic drugs or narcotic analgesics that may interfere with pain sensation; pregnancy or breastfeeding; food allergies to nuts, and so on; and participation in the other clinical trials within 30 days.

### Sample size calculation

2.3

We have demonstrated both in vitro and in vivo experiments that JCE has improved KOA and has antioxidant effects. To determine the minimum effective concentration, JCE was administered at various concentrations, and 100 mg/kg and 200 mg/kg of JCE was administered to the mice for 14 days, based on which it was confirmed that JCE had an excellent effect on improving the joint symptoms. Based on the US FDA guidelines for calculating the effective dose according to the body surface area in humans, the effective dose in the animal tests was calculated as the effective dose in terms of human body. Based on these calculations, the dose in the human body was set at 1000 mg and 2000 mg. Julius suggests that for the preliminary study and parallel design, the empirically optimal sample size is 12 persons per group, considering feasibility, estimated average, and dispersion accuracy.^[5]^ Therefore, we designed a pilot study with 12 subjects for each group.

### Randomization and blinding procedures

2.4

Randomization will be performed by stratified block randomization method in experimental groups 1 and 2 and control group at a ratio of 1:1:1 to ensure a balanced distribution of the 3 groups. Subjects who meet all registration criteria will be randomly assigned to randomization identification code (ex. KOA-R-001, KOA-R-002, …, KOA-R-036) in the order generated by a computer randomized program. The randomization identification code will indicate whether JCE 1000 mg, 2000 mg, or placebo is to be given. As this pilot study is designed to be double-blinded, the participants, researchers, and assessors collecting the data will be blinded to the group allocation.

The information of intervention assignment will be stored in the third statistical department. The randomization code will be placed in an opaque envelope and stored at the hospital. With the exception of disclosure to individual patients in emergency situations, randomization and blinding were not disclosed to researchers until the end of the trial.

### Intervention

2.5

All eligible participants will receive a treatment according to the allocated group, JCE 1000 mg, 2000 mg, or placebo, in the following 12-week treatment period. To maintain the double-blinded nature of the study, JCE 1000 mg, 2000 mg, and placebo will be manufactured to be similar in appearance, smell, and taste, and will be indistinguishable to which group the clinical trial subjects assigned. The subjects will be evaluated twice in 12 weeks (at 6 and 12 weeks). JCE 1000 mg, JCE 2000 mg, and placebo will be manufactured by Hankookshinyak Pharmaceutical Co. (Nonsan, Republic of Korea) and 2 sticks will be taken orally twice a day.

### Outcome measures

2.6

The primary outcome is Korean Western Ontario and McMaster Universities Questionnaire (K-WOMAC) score, which will be used to assess items related to knee pain, joint stiffness, and physical functioning in the 6^th^ and 12^th^ week of treatment. The secondary outcomes are pain visual analog scale score after 6 and 12 weeks of treatment, EuroQol Five Dimensions questionnaire survey score for rating quality of life, Patient's Global Impression of Change on treatment and the change of erythrocyte sedimentation rate, and C-reactive protein level, which indicated inflammation in the body. For safety of the subjects, we will conduct laboratory tests such as blood clotting factors, liver function, inflammation-related enzymes, and complete blood count, and evaluate vital signs. Safety assessments will be conducted at every visit. Participants’ data will be anonymized and coded by a specific program.

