### Statistical analysis

2.8

Statistical analysis will be primarily based on the principle of full analysis set. The missing values will be analyzed by the last observation carried forward method. For each of the 2 experimental groups and the control group, the baseline values before treatment and the changes in K-WOMAC at 6 and 12 weeks after treatment will be measured, and the descriptive statistics will include measurement of mean, standard deviation, median, minimum, and maximum. The analysis method for evaluation of the variables of efficacy involves confirmation of the normality of the values and then comparison using analysis of variance or Kruskal–Wallis test and post-test using Bonferroni method. The significance level will be set at *P* < .05 and the confidence interval at 95%. All statistical analyses will be performed using SPSS Statistics for Windows Version 20.0 (IBM Corp., Armonk, NY).

If necessary, subgroup analyses of outcome variables such as demographic variables measured at baseline (eg, sex, age, duration of illness, treatment expectation, and so on) can be performed. Safety assessments will be performed primarily by analyzing the frequency of adverse events and severe adverse events (SAEs) that researchers suspect to be related to treatment. The collected safety data will be summarized appropriately. All adverse events that occur will be listed with a detailed description. All SAEs will be recorded descriptively. The adverse events will be collected through patient symptom reporting and researcher observation. The frequency of each adverse event associated with or unrelated to the intervention will be recorded and analyzed using descriptive statistics. There is no intermediate analysis of this study, and the final decision regarding the completion of the clinical trial will be with the principal investigator.

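### K-WOMAC is primary at both week 6 and week 12 with neither deciding; testing each visit under section 2.8 gives about 7% to 10% false positives, and the abstract names a different analysis

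*Protocol article*

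**What the plan says.** Three places in the protocol article bear on this point.

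- **Section 2.6, Outcome measures.** "The primary outcome is Korean Western Ontario and McMaster Universities Questionnaire (K-WOMAC) score". The sentence goes on to say that it serves to "assess items related to knee pain, joint stiffness, and physical functioning in the 6^th^ and 12^th^ week of treatment". Both weeks carry the same weight.
- **Section 2.8, Statistical analysis.** For each group, "the changes in K-WOMAC at 6 and 12 weeks after treatment will be measured". The efficacy variables are to be checked for normality, followed by "comparison using analysis of variance or Kruskal–Wallis test and post-test using Bonferroni method". The only significance level given is P < .05. No subscale is named, and neither week is ranked first.
- **Abstract, Methods.** "The primary outcomes will be measured using Korean Western Ontario and McMaster Universities Questionnaire" (plural, where section 2.6 has the singular), and "Repeated-measure analysis will be used to measure primary efficacy based on full analysis set".

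Section 2.1 sets three groups allocated 1:1:1, 36 subjects in all. Section 2.3 gives 12 per group on a rule of thumb for pilot studies, with no effect size or power.

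**The concern.** A primary analysis should lead to one pre-stated comparison, or to several under a stated correction. Here two visits can each supply a primary result, and nothing says which one counts or what follows if they disagree. The Bonferroni step comes after the three-group test, so on its natural reading it adjusts for the pairs of groups within one test. It does not adjust for testing at week 6 and again at week 12.

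The abstract adds a second difficulty. A repeated-measure analysis could combine both visits in one test, but the section that sets out the statistics prescribes something else. A reader cannot tell which analysis carries the efficacy conclusion.

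What is at stake is the meaning of P < .05 for the primary claim. The introduction says that the trial is designed to verify efficacy. The discussion expects it to inform dosage and duration and to support further studies. If the visit or score could be chosen after the data were seen, that choice would carry over into those uses.

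**Working it through.** **Inputs from the article:** 3 groups of 12 (sections 2.1 and 2.3); level 0.05 (section 2.8); 2 post-baseline visits (sections 2.6 and 2.8); Bonferroni post-test, read as 3 group pairs (section 2.8).

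**Input not in the article:** the correlation r between the week-6 and week-12 values of the score within a group. It is assumed to lie between 0 and 0.9. Two changes measured from the same baseline are likely to be positively correlated, so r = 0 serves as the upper end of the error rate rather than as a likely value.

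**Step 1: the stated 5%, for one score at one visit.** With Bonferroni over three pairs, each pair is tested at 0.05/3, and the error over the pairs is at most 3 × 0.05/3 = 0.05. In the two-visit simulation below, the omnibus analysis of variance at a single visit rejected in 4.8% to 5.0% of null trials. The stated level therefore holds for one score at one visit.

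**Step 2: one score tested at both visits, independent case.** 1 − (1 − 0.05)² = 1 − 0.9025 = 0.0975, or 9.75%.

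**Step 3: one score tested at both visits, correlated case.** 40,000 null trials were simulated for each r, with normal data, 3 groups of 12 and a one-way analysis of variance at 0.05 for each visit. The middle column is the chance that at least one visit is significant. The last column also requires a significant Bonferroni pair at that same visit.

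| r between visits | Omnibus test, either visit | Omnibus test plus a Bonferroni pair, either visit |
|---|---|---|
| 0 | 9.8% | 8.2% |
| 0.3 | 9.3% | 7.9% |
| 0.5 | 9.0% | 7.6% |
| 0.7 | 8.3% | 7.1% |
| 0.8 | 7.7% | 6.6% |
| 0.9 | 7.1% | 6.1% |

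The simulation error is small: near 9% the standard error is √(0.09 × 0.91/40,000) = 0.0014, or 0.14 percentage points. The Kruskal–Wallis option was not simulated. The formula in step 2 applies to any two independent tests at 0.05.

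**Step 4: the alternatives.**
- One deciding score at one visit: 5%, as in step 1.
- One overall group test in a repeated-measures analysis, which is a possible reading of the abstract: a single test at 0.05, hence 5%.
- Both visits kept, with Bonferroni extended to them: 0.025 each, at most 2 × 0.025 = 0.05 (1 − 0.975² = 0.0494 if independent).

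**The case against.** **The abstract already controls the error.** One overall repeated-measures group test over both visits would hold 5%. That is correct, but section 2.8 never mentions such a test and prescribes another method. The abstract also does not say which term of the repeated-measures model decides. The objection shows that a sound analysis may have been intended. It does not show that the plan fixes one.

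**Testing at each visit is an inference.** Section 2.8 gives one general sentence on the comparison and does not say outright that each week has its own test. This stands, and so the 7% to 10% is conditional on testing both visits. It is nevertheless the natural way to apply a one-way method to a variable defined at two weeks.

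**The .05 is a significance level, not a promised family-wise rate, and the trial is a pilot.** Both are true. No success rule is stated, the sample size has no power basis, and the discussion concedes that the sample may be small. This lowers the consequence but does not tell the reader which result is primary.

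**A condensed article may leave the scoring detail to a fuller document.** For total versus subscale scores this has some force. It has less for the choice of visit, because the article defines the primary outcome in two sections and treats the weeks alike in both. It has none for the disagreement between the abstract and section 2.8.

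**A stronger reading is tempting.** A reader might infer that pain, stiffness and function are three separate primary endpoints, each tested at two visits, which would give six tests and a much larger error rate. The document does not support this. Section 2.6 names a single score and mentions the three areas only as what its items assess. Section 2.8 names no subscale, and no text prescribes a test for each domain. The plural in the abstract is loose wording for one instrument and lists no domains.

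**Conclusion.** The plan is wrong as written on this point. It names no deciding visit for the primary K-WOMAC score, leaves total versus subscale open, and applies a correction that reads as covering only the group pairs. If both visits are tested under section 2.8, the chance of at least one false-positive primary result is about 7% (r = 0.9) to 10% (r = 0). It remains 6.1% to 8.2% if a significant Bonferroni pair is also required. These figures rest on the assumed correlations, on normal data and on one score tested once per visit. The rate is above 5% throughout the range examined, but moderately so.

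Separately, and with no assumption needed, the abstract and section 2.8 name different primary analyses. In a pilot with 12 per group the overall consequence is moderate, and the correction is worth making because it is simple.

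**What to change.** - **Sections 2.6 and 2.8:** name one primary endpoint, change from baseline in K-WOMAC total score at week 12, the end of the treatment period. Make week 6 and the pain, stiffness and function subscales secondary, reported with unadjusted 95% intervals and labelled descriptive.
- **Abstract and section 2.8:** state the same primary analysis. If a repeated-measures model is kept, say which single result decides: the group comparison at week 12, or one overall group test across both visits. With the week-12 endpoint above, the week-12 comparison is the matching choice.
- **If both weeks must stay primary:** extend the Bonferroni correction to them at 0.025 each, which also holds the error at or below 5%.

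The change takes about a sentence in each place and needs no extra subjects, visits or data. The cost is that a week-6 or single-subscale result can no longer be claimed as primary.

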### Data collection and monitoring

2.7

During the screening period, the subjects will complete a questionnaire regarding their sociodemographic characteristics, provide their medical history, take a x-ray of both knee, and perform the laboratory test. Personal information and data collected during the screening period will be shared and managed by the hospital. The monitoring of data and research performances will be conducted regularly by researchers from the Jeneolurl Bio Taek Co., Ltd. (Pusan, Republic of Korea). The final trial dataset is accessible to statisticians and principal investigator. The results of this study will be published in a peer-reviewed article.

### Statistical analysis

2.8

Statistical analysis will be primarily based on the principle of full analysis set. The missing values will be analyzed by the last observation carried forward method. For each of the 2 experimental groups and the control group, the baseline values before treatment and the changes in K-WOMAC at 6 and 12 weeks after treatment will be measured, and the descriptive statistics will include measurement of mean, standard deviation, median, minimum, and maximum. The analysis method for evaluation of the variables of efficacy involves confirmation of the normality of the values and then comparison using analysis of variance or Kruskal–Wallis test and post-test using Bonferroni method. The significance level will be set at *P* < .05 and the confidence interval at 95%. All statistical analyses will be performed using SPSS Statistics for Windows Version 20.0 (IBM Corp., Armonk, NY).

If necessary, subgroup analyses of outcome variables such as demographic variables measured at baseline (eg, sex, age, duration of illness, treatment expectation, and so on) can be performed. Safety assessments will be performed primarily by analyzing the frequency of adverse events and severe adverse events (SAEs) that researchers suspect to be related to treatment. The collected safety data will be summarized appropriately. All adverse events that occur will be listed with a detailed description. All SAEs will be recorded descriptively. The adverse events will be collected through patient symptom reporting and researcher observation. The frequency of each adverse event associated with or unrelated to the intervention will be recorded and analyzed using descriptive statistics. There is no intermediate analysis of this study, and the final decision regarding the completion of the clinical trial will be with the principal investigator.

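### Carrying the last K-WOMAC value forward can bias the week-12 comparison, in either direction, if scores change after dropout; a repeated-measures model of the observed values is a cheap improvement

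*Protocol article*

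**What the plan says.** Section 2.8 (Statistical analysis) sets the population and the handling of missing data in its first two sentences: "Statistical analysis will be primarily based on the principle of full analysis set", then "The missing values will be analyzed by the last observation carried forward method". No other missing-data method appears in the article. The primary variable follows: "changes in K-WOMAC at 6 and 12 weeks after treatment will be measured". The test applied to the filled data is a "comparison using analysis of variance or Kruskal–Wallis test and post-test using Bonferroni method", and "The significance level will be set at *P* < .05".

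The Methods part of the abstract describes the primary analysis differently: "Repeated-measure analysis will be used to measure primary efficacy based on full analysis set". Section 2.8 does not describe such an analysis, and the abstract does not say what kind of repeated-measures analysis is meant.

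Section 2.1 gives the total ("A total of 36 subjects with KOA will be recruited") and section 2.3 the arm size ("Therefore, we designed a pilot study with 12 subjects for each group"). The article states no expected dropout rate, SD, effect size or time course for K-WOMAC.

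**The concern.** There are only two post-baseline measurements, at weeks 6 and 12. Carry-forward therefore does one of two things at week 12. A participant lost after week 6 is given the week-6 value. A participant lost before week 6, if kept in the analysis with baseline carried forward, is given a change of exactly zero. Both are right on average only if the mean score would not have moved after the last visit attended, and the article offers no support for that.

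Section 3 (Discussion) says that the study is meant to inform dosage and duration. Different losses by arm distort the dose contrasts, and copying week 6 into week 12 removes information on duration. Arm-related loss is possible: section 2.11 foresees participants leaving after serious adverse events or adverse drug reactions. With 12 per arm, each person lost is 1/12 = 8.3% of the arm, so a difference of two people between arms is enough to matter.

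**Working it through.** **The plan's own figure.** 3 groups × 12 = 36, which reproduces the stated total. The size rests on a rule of thumb for pilots, so there is no power calculation to reproduce.

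**Bias formula.** In one arm, let *pb* be the proportion lost before week 6 (baseline carried, change 0), *p6* the proportion lost after week 6, and *m6* and *m12* the true mean changes. With dropout unrelated to the scores,

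- carry-forward mean change = (1 − *pb* − *p6*) × *m12* + *p6* × *m6*
- bias in the arm = −*pb* × *m12* − *p6* × (*m12* − *m6*)
- bias in the contrast = bias in active − bias in placebo.

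**Simple case: the same trajectory in both arms.** The size of the bias is the difference in dropout times the change missed. Assume 3/12 against 1/12 lost, a difference of 2/12:

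- lost after week 6, 4 further points: 2/12 × 4 = 0.67
- lost after week 6, 6 further points: 2/12 × 6 = 1.0
- lost before week 6, baseline carried, 12 points of change: 2/12 × 12 = 2.0.

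**Wider set of cases (all inputs assumed; negative change is improvement).**

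| Active (wk 6/wk 12) | Placebo (wk 6/wk 12) | Dropout, active v placebo | Timing | True difference | Carry-forward | Bias |
|---|---|---|---|---|---|---|
| −10/−15 | −10/−15 | 25% v 8.3% | before wk 6 | 0 | 2.5 | 2.5 |
| −10/−15 | −10/−15 | 8.3% v 25% | before wk 6 | 0 | −2.5 | −2.5 |
| −10/−15 | −10/−15 | 25% v 8.3% | after wk 6 | 0 | 0.83 | 0.83 |
| −10/−10 | −10/−10 | 25% v 8.3% | after wk 6 | 0 | 0 | 0 |
| 0/0 | 0/0 | 25% v 8.3% | before wk 6 | 0 | 0 | 0 |
| −12/−20 | −8/−10 | 16.7% v 16.7% | before wk 6 | −10 | −8.33 | 1.67 |
| −12/−20 | −8/−10 | 16.7% v 16.7% | after wk 6 | −10 | −9.0 | 1.0 |
| −12/−20 | −8/−10 | 25% v 8.3% | before wk 6 | −10 | −5.83 | 4.17 |

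Rows 1 and 2 show that the sign follows the arm that loses more. Rows 4 and 5 show that unequal dropout alone gives no bias when the mean does not move after the last visit. Rows 6 and 7 show bias with equal dropout when the trajectories differ.

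**Standard error and coverage.** These come from 20,000 simulated trials per case: 12 per arm, assumed SD 15 per visit and correlation 0.6, dropout completely at random, and a pairwise pooled t interval at two-sided 0.05 without Bonferroni adjustment (the article does not state sidedness).

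- No true difference (row 1): carry-forward rejects in 7.9% and covers in 92.1%; completers reject in 5.1% and cover in 94.9%.
- No true difference, loss after week 6 (row 3): carry-forward rejects in 5.2%.
- True difference −10 (row 8): carry-forward covers in 88.5% and rejects in 15.5%; completers cover in 95.0% and reject in 34.2%.
- Model SE against completers: 5.65 v 6.10 in row 8 (7% smaller), and 5.16 v 6.44 with 25% lost in both arms, half before and half after week 6 (20% smaller).
- Model SE against the carry-forward estimator's own sampling SD (row 1): 5.46 v 5.51, so the two agree.

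The benchmark here is the analysis of observed completers. A mixed model was not simulated.

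**The case against.** The case for leaving the plan alone has several parts, and much of it stands.

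- A reader might infer that carry-forward biases the result whenever dropout differs by arm. The table shows otherwise: unequal dropout is neither sufficient nor necessary. Bias needs a mean score that changes after the last observed visit. That scores keep changing after week 6 is an assumption, since the article gives no trajectory.
- A reader might infer that the standard error understates the variability of the carry-forward estimate. It does not; it matches that estimator's own sampling SD. It is smaller than the observed data support because filled values count as data, and the poor coverage comes from bias.
- A reader might infer that the abstract already plans a mixed model that needs no filling. It says only that the analysis is of repeated measures. A classical repeated-measures ANOVA would need complete or filled data.
- The 2.0-point case, and every case with loss before week 6, needs baseline to be carried forward. Section 2.8 neither says so nor defines the full analysis set, and section 2.9 says that withdrawn participants are excluded from the study. If a post-baseline value is required, these cases fall away and the simple range ends at 1.0 point.
- Against an SE of about 5.5 (assumed SD 15), 0.67 to 2.0 points is 12% to 36% of one SE. The trial is a pilot without a power target, and its Discussion concedes that the sample is small.
- The lack of a missing-not-at-random sensitivity analysis cannot be held against the article, because an analysis plan that is not shown may contain one.

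What does not stand is the idea that an unseen plan settles the matter. Carry-forward is a rule that the article states, not a detail that it leaves open.

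**Conclusion.** The concern holds in a limited form. Section 2.8 fixes a missing-data rule that assumes no change in K-WOMAC after dropout. Where that assumption fails, the week-12 contrast is biased, in either direction, when dropout or trajectories differ by arm, and the standard error reflects more data than were observed.

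The size cannot be established from the article. The illustrative range is about 0.7 to 1.0 points for losses after week 6 and about 2.0 points for losses before week 6 with baseline carried forward. The 4.17-point case needs an assumed true difference of 10 points as well as unequal early loss. Treating this as an error that must be corrected before the trial can be interpreted would go beyond what the documents support. For a pilot of 12 per arm it is a recommended, inexpensive improvement.

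**What to change.** In section 2.8, and in the analysis plan if there is one, make the primary analysis a likelihood-based repeated-measures mixed model of the observed week-6 and week-12 K-WOMAC values, valid under missing-at-random, with the week-12 contrasts read from that model. Keep carry-forward at most as a supplementary analysis, and say whether it carries baseline. Reconcile section 2.8 with the abstract so that both name the same primary analysis, and name the model, because the abstract's wording does not. A sensitivity analysis under missing-not-at-random (placebo-based multiple imputation or a delta shift) is an optional addition.

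The change should be made before unblinding. It costs wording and a little programming, with no extra participants or visits. Intervals will be somewhat wider; as a rough guide, the completer SE in the simulation was about 6.1 against about 5.5 under carry-forward.

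### Section 2.8 tests the groups without baseline K-WOMAC as a covariate, and the Abstract names a different analysis that does not say how baseline enters; one baseline-adjusted model would be more precise

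*Protocol article*

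**What the plan says.** **Outcome.** Under Outcome measures (2.6), "The primary outcome is Korean Western Ontario and McMaster Universities Questionnaire (K-WOMAC) score", assessed at weeks 6 and 12.

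**Use of baseline.** Section 2.8 states that for each group "the baseline values before treatment and the changes in K-WOMAC at 6 and 12 weeks after treatment will be measured", and lists descriptive statistics for them.

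**Test.** Section 2.8 then describes a normality check followed by "comparison using analysis of variance or Kruskal–Wallis test and post-test using Bonferroni method". No baseline covariate and no stratification factor is named. The text does not say whether the values tested are raw scores or changes.

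**Abstract.** Its Methods paragraph names something else: "Repeated-measure analysis will be used to measure primary efficacy based on full analysis set". It does not say whether baseline is a covariate, a time point or absent.

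**Randomisation.** Section 2.4: "Randomization will be performed by stratified block randomization method in experimental groups 1 and 2 and control group at a ratio of 1:1:1". The stratification factors are not named.

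**Size.** Section 2.3: "Therefore, we designed a pilot study with 12 subjects for each group". The number rests on a rule of thumb for pilot studies; no effect size, SD or power is given.

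**The concern.** A pre-treatment K-WOMAC is collected, but the efficacy test in Section 2.8 does not use it as a covariate. A Kruskal–Wallis test cannot carry one, and a one-way ANOVA as written does not. Subtracting baseline is the same as fixing its slope at 1, whereas the best slope for two measurements of equal variance is their correlation, which is below 1. The result is a larger standard error than necessary.

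With 12 patients per arm, chance baseline differences can be sizeable. An arm that starts worse by chance tends to show more improvement on change scores through regression to the mean; raw follow-up scores err the other way. Covariate adjustment deals with both.

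The two descriptions of the primary analysis also have to be reconciled before anyone can say which model is planned. A pilot meant to lay the ground for further studies will be read mainly for its estimates and intervals, so their width matters even without a power claim.

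**Working it through.** **Inputs from the article.** 12 per arm, three arms, 36 in total (2.1, 2.3); significance level 0.05 (2.8).

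**Assumptions, not in the article.** Two-sided testing; Bonferroni over three pairs, so 0.05/3 = 0.0167; equal variance at baseline and follow-up; complete data; baseline-to-follow-up correlation rho from 0.3 to 0.8.

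**The plan's own figure.** 3 × 12 = 36 reproduces. There is no power calculation to check.

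**Chance imbalance.** The SD of the baseline difference between two arms is sqrt(2/12) = 0.41 patient-level SD.

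**Variance of a two-arm difference**, in units of (2/12) × SD²:
- raw follow-up score: 1
- change score: 2(1 − rho)
- ANCOVA: (1 − rho²) × (1 + 1/32). The last factor is the average cost of estimating one covariate slope with 36 patients.

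Example at rho 0.5: the change score gives 2 × 0.5 = 1.00; ANCOVA gives 0.75 × 1.03125 = 0.773. The ratio is 0.77, and 12/0.773 = 15.5 per arm.

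| rho | change score | ANCOVA | ANCOVA / change | ANCOVA / raw | n per arm to match ANCOVA with 12: change | same: raw |
|---|---|---|---|---|---|---|
| 0.3 | 1.40 | 0.938 | 0.67 | 0.94 | 17.9 | 12.8 |
| 0.5 | 1.00 | 0.773 | 0.77 | 0.77 | 15.5 | 15.5 |
| 0.7 | 0.60 | 0.526 | 0.88 | 0.53 | 13.7 | 22.8 |
| 0.8 | 0.40 | 0.371 | 0.93 | 0.37 | 12.9 | 32.3 |

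**Power for one pairwise contrast.** Noncentral t with pooled error, df 33 unadjusted and 32 for ANCOVA, noncentrality = difference / sqrt(variance factor × 2/12). For a true difference of 0.8 SD at rho 0.5, the noncentrality is 0.8/sqrt(0.1667) = 1.96 unadjusted (raw and change scores coincide at this rho) and 0.8/sqrt(0.773 × 0.1667) = 2.23 for ANCOVA.

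| rho | level | change score | ANCOVA |
|---|---|---|---|
| 0.5 | 0.05 | 48% | 58% |
| 0.5 | 0.0167 | 30% | 40% |
| 0.8 | 0.05 | 85% | 88% |
| 0.8 | 0.0167 | 72% | 75% |

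As a check, simulation with 10,000 runs for a 1 SD difference at 0.0167 gave change-score and ANCOVA power of 34% and 51% (rho 0.3), 47% and 61% (rho 0.5), and 73% and 80% (rho 0.7), within about one point of the formula.

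**Strata.** No calculation is possible. The factors, their number and their prognostic value are not given.

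**The case against.** The strongest reply is that the article does not settle on one unadjusted test: the Abstract's repeated-measure analysis could use baseline as a time point or covariate. That stands as a reason to reconcile the two places first. It does not answer the point, because the Abstract does not say how baseline enters and the detailed section names another test.

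It can also be said that covariates are commonly left to the analysis plan. That would hold if the article were silent, but Section 2.8 names specific tests.

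Third, this is a pilot sized for feasibility and for estimating means and dispersion, with an admitted small sample. That stands as a limit on severity: no stated figure is wrong.

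Four stronger readings are tempting but unsupported:
- *Baseline is ignored.* Section 2.8 refers to changes, so baseline probably enters by subtraction.
- *Change scores are biased.* Over randomisation they are unbiased; imbalance distorts them only conditionally on the realised allocation, in either direction.
- *Omitting the strata inflates the standard error by a known amount.* This depends on the unnamed factors being prognostic, and with 36 patients many strata would themselves cost degrees of freedom.
- *Baseline is taken at visit 2 before the first dose.* The Abstract lists visits 2 to 4 for assessment and Section 2.1 says "the efficacy and the safety will be assessed at the 3^rd^ and 4^th^ visits". Neither ties the baseline to a visit; Section 2.8 says only that it precedes treatment. That mismatch is a separate reporting matter.

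**Conclusion.** The point holds as an avoidable loss of precision. Under either reading of the values tested, baseline adjustment has the smaller variance at every correlation tried, after paying for the covariate. Against change scores the saving runs from 33% at rho 0.3 to 7% at rho 0.8; against raw scores it runs from 6% to 63%. For a 0.8 SD difference at rho 0.5 the power gain is about 10 points; at rho 0.8 it is only about 3 points over change scores. These sizes rest on assumed correlations and equal variances, and the 0.0167 level on an assumption of three pairs. The direction does not depend on a particular rho within the range shown. No gain is claimed for the strata.

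**What to change.** 1. Make the Abstract and Section 2.8 name the same primary model: an ANCOVA, or a mixed model over both visits, for K-WOMAC at weeks 6 and 12 with baseline K-WOMAC as covariate.
2. Report adjusted mean differences between arms with confidence intervals.
3. Name the stratification factors in Section 2.4, and include them in the model if they are few.
4. Adjust pain VAS, EQ-5D, ESR and CRP for their own baselines in the same way. Where residuals are clearly non-normal, as may happen with ESR and CRP, use a transformation or a rank-based ANCOVA in place of the Kruskal–Wallis route.

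The cost is a change of wording, one degree of freedom for baseline and those for any strata included. No extra data or patients are needed, since the baseline K-WOMAC is already collected.
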